#### Secondary outcomes

*Health-related quality of life―general* will be assessed using the Dutch validated European Organisation for Research and Treatment of Cancer (EORTC) Quality of Life Questionnaire (QLQ-C30) [44]. This 30-item questionnaire includes five functional scales, three symptom scales, a global health and quality of life scale, and several single-item symptom measures. All items will be scored on a four-point Likert scale, except for the global health and quality of life scale that is scored on a seven-point linear analogue scale. After linear transformation, all scales and single-item measures range in score from 0 to 100. Higher scores on functional and health and quality of life scales indicate better functioning or HRQoL, whereas higher scores on symptom scales indicate more symptoms.

*Health-related quality of life―lymphoma-specific* will be assessed with the EORTC disease-specific modules, i.e. QLQ-HL27 for HL, QLQ-NHL-HG29 for high-grade NHL and QLQ-NHL-LG20 for low-grade NHL, and QLQ-CLL17 for CLL [45]. The modules are divided into multi-item subscales including symptom burden, physical condition/fatigue, worries/fears, health and functioning, emotional impact, and neuropathy (only in the NHL-HG29 module). Items are scored on a four-point Likert scale. After linear transformation, all scales range in score from 0 to 100, whereby a higher score reflects more problems [45].

*Self-efficacy* with regard to symptoms (in this study as a result of lymphoma) will be measured with the Self-efficacy Scale (SE28) [46–48]. This scale consists of seven items, which will be scored on a four-point Likert scale. A higher score reflects a greater sense of control. This scale had previously been used to assess self-efficacy concerning post-cancer fatigue [49].

*Adjustment to cancer* will be assessed using the 40-item Mental Adjustment to Cancer Scale (MAC) [50]. Items are rated on a four-point Likert scale. The summary scales (i.e. summary positive adjustment scale, summary negative adjustment scale) can be used to identify general adjustment styles for cancer. The summary positive adjustment scale includes 17 items and scores range from 17 to 68 (cut-off ≥47), whereas the summary negative adjustment scale includes 16 items with scores ranging from 16 to 64 (cut-off ≥36) [51]. Summary scales are scored through addition of the items.

*Illness perceptions* will be assessed using the validated Brief Illness Perception Questionnaire (B-IPQ) [52]. This scale has nine items, measuring cognitive representations, emotional representations, and illness comprehensibility. Items are scored on a continuous linear 0–10-point scale. A higher score reflects a more threatening view of the illness. The B-IPQ has been previously cross-culturally adapted into the Dutch Language Version (Brief IPQ-DLV), with acceptable face and content validity [53].

*Fatigue* will be assessed with the 20-item validated Multidimensional Fatigue Inventory (MFI) [54]. The MFI covers five scales: general fatigue, physical fatigue, reduced activity, reduced motivation, and mental fatigue. Each scale contains four items, with two items formulated in a positive (e.g. ‘I feel fit’) and two formulated in a negative direction (e.g. ‘I feel fatigued’). All items are scored on a five-point Likert scale. The negatively formulated items must be recoded before adding up scores. Higher sum scores correspond to more acute levels of fatigue. The MFI is reliable and valid to assess fatigue in patients with cancer [54].

*Health care use* will be assessed by single items: ‘How often did you contact a general practitioner in the past 12 months?’, ‘How many of these visits were related to cancer of the consequences of your cancer?’, ‘How often did you visit a medical specialist in the past 12 months?’, ‘How many of these visits were related to cancer or to the consequences of your cancer?’ These questions were asked in a similar way as by Statistics Netherlands [55] (http://statline.cbs.nl/). Three questions are asked about follow-up appointments (whether or not receiving follow-up appointment, the frequency of follow-up appointments, and satisfaction with this frequency). Furthermore, patients are asked whether they visited a psychologist, psychiatrist or social worker and the last question was ‘Did you receive care after the treatment of your cancer?’ To answer this question, patients could either choose ‘No’ or ‘Yes’ and then choose multiple additional care services from a list: sexologist, pastoral care, dietician, physical therapist, oncological rehabilitation, creative therapy, oncology nurse, or contact with other cancer survivors.

#### Covariates

*Comorbidity* at the time of survey will be assessed with the adapted Self-administered Comorbidity Questionnaire (SCQ) [56]. Patients will be asked to identify comorbid conditions that have developed since diagnosis.

*Personality* will be assessed using the Big Five Inventory (BFI) [57]. The BFI is a 44-item inventory designed to measure the Big Five dimensions: extraversion, agreeableness, conscientiousness, neuroticism, and openness to experience. Items are scored on a five-point Likert scale. Scale scores will be created by averaging the items for each domain. The Dutch BFI has good psychometric quality [58].

#### Usage statistics

In addition to the standardised questionnaires, technical data on the use of the intervention, such as frequency, duration, and activity, will be evaluated.

### Sample size calculation

Sample size calculation was performed using G*Power version 3.1.9.2 for Windows. Based on the three primary outcomes of this trial, effect on patient level is defined as increased self-management skills or satisfaction with information (as measured by the heiQ^TM^ and the ISQ, respectively) or reduced psychological distress (as measured with the HADS). Therefore, effectiveness of LIVE is demonstrated when one of the three effects is statistically significant. Significance level of the sample size calculation was adjusted to *p* ≤ 0.167 to keep the overall chance for type-I errors at 5%.

Clinically important differences will be determined with Norman’s ‘rule of thumb’, whereby a difference of approximately 0.5 SD indicates a threshold of discriminant change in quality of life scores of a chronic illness [59]. To detect a clinically important difference with 90% power, a sample size of 222 patients with lymphoma (74 in each group) is needed. This sample size calculation is based on a medium effect size of 0.25 for repeated measures analysis of variance (ANOVA) with two measurements, since at least two measurements are necessary to compare preintervention and postintervention outcomes. We take into account a response rate of 70% as observed in earlier studies (of them 60% are expected to complete the questionnaires online) and a study dropout rate of 25%, based on a systematic review on adherence to Internet interventions for anxiety and depression [60]. This results in 663 patients with lymphoma who need to be invited for participation.

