### Randomisation

Patients who complete the baseline questionnaire online and consent to participate in the LIVE trial will be automatically randomised in an equal ratio (1:1:1) to one of the three study arms: (1) standard care, (2) standard care plus access to PRO feedback or (3) standard care plus access to PRO feedback and the *Living with lymphoma *intervention. This randomisation will be performed using block randomisation. The randomisation will be performed by a computer randomisation program which will ensure a balance in sample size across groups over time [29].

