### Statistical analyses

All statistical analyses will be performed using Statistical Analyses Software (SAS; version 9.4 for Windows, SAS Institute Inc., Cary NC, USA). Analyses on effectiveness of the intervention will be primarily done according to intention-to-treat methodology. Second, per-protocol analysis will be performed to analyze the efficacy of the intervention. All statistical tests will be two-sided and considered significant if *p* < 0.05.

Missing outcome data will be assumed to be ‘missing at random’ (MAR), conditional on key predictors of ‘missingness’ (in particular, baseline values of the outcome variables of interest, and study arm).

Patients’ sociodemographic and clinical variables will be compared at baseline between the three study arms using chi-square analyses for categorical variables and ANOVA for continuous variables and will be analysed as covariates.

Repeated measures analysis using generalised estimating equations, which account for the intra-patient dependency of the repeated measures, will be used to analyse the effect of the intervention on the outcome variables. We will investigate differences in effect of the two intervention arms and the arm receiving standard care at the different time points. Differential effects of the intervention arms by age, cancer subtype, and baseline levels of the outcomes of interest will be assessed for the outcome measures by adding terms for the interaction between age, cancer subtype, baseline levels, and care arm to the regression models.

Routinely collected data from the population-based NCR on patient and tumour characteristics will enable us to compare paper-and-pencil respondents with online respondents, as well as respondents with nonrespondents and patients with unverifiable addresses in order to determine the external validity of the results and answer our second study objective.

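### The adjusted significance level is printed as 0.167, ten times 0.05/3; it cannot hold overall error at 5%, does not give the stated 222 patients, and the analysis section applies no adjustment

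*Protocol article*

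**What the plan says.** The Sample size calculation section of the protocol article names self-management skills, satisfaction with information and psychological distress as primary outcomes. Its success rule is that "effectiveness of LIVE is demonstrated when one of the three effects is statistically significant". The next sentence gives the adjustment: "Significance level of the sample size calculation was adjusted to *p* ≤ 0.167 to keep the overall chance for type-I errors at 5" per cent.

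The same section then states: "To detect a clinically important difference with 90% power, a sample size of 222 patients with lymphoma (74 in each group) is needed". That figure is "based on a medium effect size of 0.25 for repeated measures analysis of variance (ANOVA) with two measurements". The correlation between the two measurements is not given.

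The Statistical analyses section sets one threshold for the whole trial: "All statistical tests will be two-sided and considered significant if *p* < 0.05". It mentions no adjustment for the three primary outcomes. The value 0.0167 appears nowhere in the article.

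**The concern.** When one success out of three is enough, each test has to be stricter than 5% if the overall error is to stay at 5%. The printed level goes the other way: a single test at 0.167 already has a false-positive rate of 16.7%. The sentence therefore contradicts itself.

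Two things depend on it. The first is whether the sample size can be traced to its stated inputs. The second is which threshold defines success. This sentence is the only multiplicity adjustment in the article. With a wrong number here and an unadjusted one in the analysis section, a reader finds no printed threshold that meets the 5% aim.

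**Working it through.** **Inputs from the article.** Three primary outcomes, any one sufficient; overall target 5%; printed level 0.167; effect size f = 0.25; two measurements (m = 2); three arms in equal ratio (k = 3); 90% power; N = 222. **Assumptions.** One test per primary outcome; the correlation between the two measurements (ρ), which is not stated, so a range is shown; the correlation between outcomes, likewise shown as a range.

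**1. The adjusted level.** Bonferroni: 0.05/3 = 0.0167. Šidák: 1 − 0.95^(1/3) = 0.0170. The printed 0.167 follows from neither. Three times 0.167 is 0.501, so it is the Bonferroni level for an overall error of 50%, not 5%.

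**2. Overall error under the any-one-of-three rule.** For independent outcomes it is 1 − (1 − a)³:
- a = 0.167: 1 − 0.833³ = 42.2%
- a = 0.05: 1 − 0.95³ = 14.3%
- a = 0.0167: 1 − 0.9833³ = 4.9%

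For correlated outcomes the figures come from simulating three equally correlated two-sided z-tests:

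| Level per outcome | independent | correlation 0.3 | 0.5 | 0.7 |
|---|---|---|---|---|
| 0.167 | 42.2% | 40.2% | 37.2% | 32.4% |
| 0.05 | 14.3% | 13.6% | 12.5% | 10.9% |
| 0.0167 | 4.9% | 4.8% | 4.5% | 4.0% |

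**3. Reproducing the 222.** For the between-groups test in repeated-measures ANOVA, the noncentrality is λ = f²·N·m / (1 + (m − 1)ρ) = 0.0625 × 2N / (1 + ρ), with k − 1 = 2 and N − 3 degrees of freedom. The smallest N (a multiple of three) with at least 90% power is:

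| Level | ρ = 0 | 0.3 | 0.5 | 0.7 | 0.8 | 1 (same as one-way ANOVA) |
|---|---|---|---|---|---|---|
| 0.167 | 72 | 93 | 108 | 123 | 129 | 144 |
| 0.05 | 105 | 135 | 156 | 177 | 186 | 207 |
| 0.0167 | 132 | 171 | 198 | 222 | 234 | 261 |
| 0.0083 | 150 | 192 | 222 | 252 | 264 | 294 |

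At 0.167 the group-by-time interaction needs 72 or fewer for ρ from 0 upward. So no correlation from 0 to 1 gives 222 at the printed level.

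The same point in terms of power: at N = 222 and ρ = 1, the least favourable case, λ = 27.75/2 = 13.9 and power at 0.167 is 97.8%, not 90%.

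At 0.0167 and ρ = 0.7, λ = 27.75/1.7 = 16.3 and power is 90.2%, which matches. At 0.0083 and ρ = 0.5, power is 90.3%, which matches too.

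**The case against.** The strongest reply is that this is a typing slip with no effect on the design. The sentence states its aim and the one before it names three effects, so a reader can recover 0.05/3. The sample size was evidently not computed at 0.167. The sentence also concerns the sample size calculation only; the analysis has its own rule of p < 0.05, and nothing directs anyone to test at 0.167.

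Much of this stands, and it rules out three stronger readings that a reader might infer:

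- *That the trial will run at 42% overall error.* The article does not plan tests at 0.167. The 42% shows only that the sentence cannot be true; it does not describe the planned analysis, and it assumes independent outcomes.
- *That the trial is too small because of this figure.* An N of 222 exceeds anything 0.167 would require, so the slip does not show that.
- *That 222 proves 0.0167 was entered.* The match needs ρ = 0.7, which is not in the article. At 0.0167 the requirement runs from 171 to 234 for ρ from 0.3 to 0.8, and another level with another ρ also gives 222. The calculation excludes 0.167 but does not identify the level used.

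The reply does not remove the point itself. The figure is wrong as printed and nothing in the article corrects it. Reading it silently as 0.0167 still leaves the analysis section at 0.05. Nor is this detail left to a fuller document: two thresholds are stated, and neither agrees with the stated 5%.

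**Conclusion.** The point holds as an error in a stated figure, together with an unreconciled threshold in the analysis section. The printed level is too large by a factor of ten, most probably through a misplaced decimal, and it is incompatible with N = 222 at 90% power whatever non-negative correlation is assumed.

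The practical exposure lies in the analysis threshold. Taken as printed, p < 0.05 with the one-of-three rule gives about 14% overall error for independent outcomes and about 11% at a correlation of 0.7, against a stated 5%. These figures assume one test per outcome. Correcting 0.167 alone would leave them unchanged.

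**What to change.** In Sample size calculation, replace 0.167 with 0.0167, written as 0.05/3. Check the sample size record to confirm that 222 was computed at that level; if another level was used, state that one. In Statistical analyses, say that the three primary outcomes are each tested at 0.0167 and that 0.05 applies to the remaining tests.

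The edit is one number and one sentence. The real cost is a stricter threshold per outcome than the 0.05 now printed. With 222 patients and f = 0.25, and with ρ = 0.5 assumed, power for the between-groups test falls from 97.6% at 0.05 to 93.9% at 0.0167. It is 90.2% at 0.0167 if ρ is 0.7. At ρ = 0.8 the requirement would be 234, slightly above 222.

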## Methods/design

### Objectives and hypotheses

The objective of the LIVE trial is to examine whether PRO feedback and the* Living with lymphoma *intervention will increase self-management skills and satisfaction with information and reduce psychological distress. In concordance with the stress-coping model of Lazarus and Folkman (1984), psychological adjustment after cancer is determined by the balance between stress and resources [18]. Therefore, it is hypothesised that patients with access to PRO feedback and/or the *Living with lymphoma *intervention will report increased self-management skills and satisfaction with information (greater resources available for coping), and lower levels of psychological distress compared to patients receiving standard care. Moreover, it is expected that patients with access to both PRO feedback and the *Living with lymphoma *intervention will benefit most.

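### The 90% power is claimed for 0.5 SD, but an ANOVA effect size of 0.25 across three equal arms means 0.53 to 0.61 SD between the extreme arms

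*Protocol article*

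**What the plan says.** All the figures stand in the protocol article under Sample size calculation.

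- **Threshold.** Citing a published rule of thumb, the article holds that "a difference of approximately 0.5 SD indicates a threshold of discriminant change in quality of life scores of a chronic illness".
- **Claim.** "To detect a clinically important difference with 90% power, a sample size of 222 patients with lymphoma (74 in each group) is needed".
- **Input.** "This sample size calculation is based on a medium effect size of 0.25 for repeated measures analysis of variance (ANOVA) with two measurements".
- **Alpha.** Printed as "≤ 0.167 to keep the overall chance for type-I errors at 5" per cent, because a significant effect on any one of three primary outcomes counts as success.

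Under Randomisation, patients "will be automatically randomised in an equal ratio (1:1:1) to one of the three study arms". Under Objectives and hypotheses, both intervention arms are expected to do better than standard care, and patients with PRO feedback plus the Living with lymphoma "intervention will benefit most".

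The comparisons of interest are between arms. Study design sets arm 3 against arm 2 and arm 1. Statistical analyses says "We will investigate differences in effect of the two intervention arms and the arm receiving standard care at the different time points". The Discussion speaks of superiority of each intervention package over standard care.

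The article does not state the correlation between measurements, the assumed pattern of arm means, or which ANOVA effect was powered.

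**The concern.** The threshold, power, sample size and effect size appear together as one calculation, so a reader will take 0.25 to be the ANOVA form of 0.5 SD. That conversion, f = d/2, belongs to two equal groups, and this trial has three. An N solved for 90% power at f = 0.25 therefore has less than 90% at 0.5 SD.

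At stake is how a non-significant result will be read. If the article's 90% is taken at face value, a missed 0.5 SD difference looks like good evidence of no effect. The stated power also belongs to an overall three-arm test, not to the comparisons to be reported. The comparison most exposed is arm 3 versus arm 2, the only one that isolates Living with lymphoma.

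**Working it through.** **Inputs.** From the article: three arms, 1:1:1; N = 222 (74 per arm); power 90%; effect size 0.25, read as Cohen's f, the effect size for ANOVA in the software named; m = 2 measurements; two-sided tests; threshold 0.5 SD. Assumed: alpha = 0.05/3 = 0.0167, because the printed 0.167 cannot hold three tests to 5% overall; correlation r of 0.5 to 0.7 between measurements.

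**Step 1: reproduce the 222.** For the between-arm effect in repeated measures ANOVA, the noncentrality is lambda = N f² m / (1 + (m − 1) r), with 2 and N − 3 degrees of freedom.
- r = 0.7: lambda = 222 × 0.0625 × 2 / 1.7 = 16.32; critical F(2, 219) = 4.17; power 90.2%. The smallest multiple of 3 that reaches 90% is exactly 222.
- r = 0.5: 198 would be enough.

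A 1-df test with lambda = N f² needs 220, or 222 as a multiple of 3. The source of 222 is therefore inferred, not known.

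**Step 2: convert f to SD units.** f is the SD of the arm means (divisor k, the number of arms) divided by the within-arm SD. Let d be the gap between the extreme arms.

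| Pattern | f as a function of d | f at d = 0.5 | d at f = 0.25 |
|---|---|---|---|
| Two equal groups | d/2 | 0.250 | 0.50 |
| Three arms, one differs (0, 0, d) | d√2/3 | 0.236 | 0.53 |
| Three arms, evenly spaced (0, d/2, d) | d/√6 | 0.204 | 0.61 |

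For a fixed gap between the extreme arms, the second row gives the largest f and the third the smallest.

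**Step 3: power at a true 0.5 SD gap, N = 222, alpha 0.0167.**

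| r | One arm differs | Evenly spaced | N for 90% power |
|---|---|---|---|
| 0.7 | lambda 14.51, 85.7% | lambda 10.88, 71.7% | 249 / 330 |
| 0.5 | lambda 16.44, 90.4% | lambda 12.33, 78.2% | 222 / 294 |

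The r = 0.5 row reaches 90% only because 222 exceeds the 198 that f = 0.25 would need there. If N is instead solved for 90% at f = 0.25 for each correlation (132, 171, 198 and 222 at r = 0, 0.3, 0.5 and 0.7), power at 0.5 SD is about 86% or 72% each time.

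**Step 4: pairwise power.** Two-sample noncentral t, 74 per arm, two-sided alpha 0.0167, noncentrality (d/s) × √(74/2). Here s = √(2(1 − r)) for a change score and s = √(1 − r²) for a baseline-adjusted comparison.

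| True gap | Analysis | r = 0.5 | r = 0.7 |
|---|---|---|---|
| 0.5 SD | Change score | 73% | 93% |
| 0.5 SD | Baseline-adjusted | 86% | 97% |
| 0.25 SD | Change score | 19% | 33% |
| 0.25 SD | Baseline-adjusted | 26% | 39% |

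The 0.25 SD rows show arm 3 versus arm 2 if the effects were evenly spaced over 0.5 SD. The alpha of 0.0167 allows for three outcomes, not for several contrasts within an outcome.

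**The case against.** The case for leaving the text alone has several parts.

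- **The link from 0.25 to 0.5 SD is implied.** The article calls 0.25 a medium effect size and never writes the conversion. This softens the point only a little, because the 90% is claimed explicitly for a clinically important difference and 0.5 SD is the only definition given.
- **Even spacing is not stated.** The hypotheses rank arm 3 first but give no distances. Even spacing is the least favourable pattern for a given gap. If arm 2 gained 0.5 SD and arm 3 gained 0.56 SD, f would be 0.251 and power 90.4% at r = 0.7. This stands: 72% is a worst case, not a prediction. The extreme arms there are 0.56 SD apart, though, so the example agrees with a detectable range of 0.53 to 0.61 SD.
- **The correlation is unknown.** At r = 0.5 the one-arm-differs pattern does reach 90%. This also stands, and the result must be quoted as a range.
- **Pairwise power may be adequate.** At r = 0.7, a 0.5 SD contrast has 93% to 97%. This is correct, and it is why the remedy is a restatement.

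A reader might infer two stronger things that the document does not support. The first is that 222 can only have come from the between-arm option, so the wrong test was powered. Step 1 shows another route to 222. For the arm-by-time interaction, the required N depends on the software's effect-size option: at alpha 0.0167 it is 69 at r = 0.5 under the default and 261 under the alternative. The article does not say which was used. The second is that the trial is too small and must recruit more. The pairwise figures do not show that for a 0.5 SD contrast.

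**Conclusion.** The power statement is wrong as written, by a modest to material amount. The conversion is exact and needs no assumption beyond reading 0.25 as Cohen's f: with three equal arms, 0.5 SD between the extremes is an f of at most 0.236, so a calculation at 0.25 does not deliver its stated power at 0.5 SD. The size of the shortfall is less certain. Over correlations of 0.5 to 0.7, with alpha taken as 0.0167 and the between-arm F test, power at N = 222 runs from 72% to 90%, depending on the pattern of arm means.

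Separately, the calculation that reproduces 222 is an omnibus test and does not give the power of the arm-against-arm comparisons the article describes. For a full 0.5 SD these range from 73% to 97%. For an increment of 0.25 SD between arms 3 and 2 they are low, at 19% to 39%. This calls for a corrected claim. It does not show that the sample size is inadequate.

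**What to change.** Keep N at 222 and correct the claim in one of two ways.

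1. State that 222 patients give 90% power for f = 0.25 in an omnibus three-arm test, which is 0.53 SD between the extreme arms if one arm differs and 0.61 SD if they are evenly spaced. Give the correlation, the tested effect and the alpha actually used, and reconcile the printed 0.167 with the 5% overall error.
2. Replace the claim with power for each pairwise 0.5 SD contrast at 74 per arm and two-sided alpha 0.0167, under the analysis intended and over a stated range of correlations (Step 4).

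With either, add that arm 3 versus arm 2 has low power for an increment smaller than 0.5 SD, with the 0.25 SD figures as the example, so that a null result there is not read as no added benefit.

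The cost is a re-run of the calculation and a few sentences. No patients are added. The stated power becomes less favourable in some settings.

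### The 663 invitations do not deliver the 222 patients needed: at the plan's own rates they yield about 209 completers

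*Protocol article*

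**What the plan says.** Everything needed stands in the article's section on sample size calculation. The target is stated as "a sample size of 222 patients with lymphoma (74 in each group) is needed", for the purpose given as "To detect a clinically important difference with 90% power". The calculation rests on a "medium effect size of 0.25 for repeated measures analysis of variance (ANOVA) with two measurements".

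The section then moves from 222 to a number of invitations. It allows for a 70% response rate, for 60% of responders completing the questionnaires online, and for "a study dropout rate of 25" per cent. The result is given as "This results in 663 patients with lymphoma who need to be invited for participation". The intermediate numbers and the inflation formula are not shown.

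The Recruitment and Randomisation sections fix the order of the losses. Patients who choose paper questionnaires cannot enter the trial. Those who complete baseline online and consent are "automatically randomised in an equal ratio (1:1:1) to one of the three study arms". The 60% therefore applies before randomisation and the 25% after it.

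**The concern.** An allowance for dropout should ensure that the number left after dropout equals the number required. If a fraction d is lost, the number to start with is n/(1 − d). Using n × (1 + d) gives too small a number, and the gap widens as d grows: at d = 0.25 the two factors are 1.333 and 1.25.

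Running 663 forward through the three stated rates gives fewer than 222, so the invitation figure and the required sample size are inconsistent. The error lies in the unsafe direction. If recruitment were planned around 663 and every forecast came true, the trial would end below the number that the article says is needed for 90% power. The article gives the trial status as recruiting, so the figure was still in use when it was published.

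**Working it through.** **Inputs, all from the sample size section:** required number 222 (74 × 3); response 0.70; online among responders 0.60; dropout 0.25; stated invitations 663. The fraction of invited patients who reach randomisation is 0.70 × 0.60 = 0.42.

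**1. Reproducing the plan's figure.** Multiply for dropout, then divide by the other two rates, rounding up at each step:
- 222 × 1.25 = 277.5, rounded up to 278
- 278 / 0.60 = 463.3, rounded up to 464
- 464 / 0.70 = 662.9, rounded up to 663

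This matches exactly. Without stepwise rounding the same route gives 661 to 662.

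**2. Running 663 forward.**
- Randomised: 663 × 0.42 = 278.5, about 278
- Completing: 278.5 × 0.75 = 208.8, about 209
- Per arm: 209 / 3 = about 70, against 74
- Shortfall: 222 − 209 = 13, and 13 / 222 = 6%

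This step does not depend on how the sponsor obtained 663.

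**3. Correct inflation.**
- Randomised: 222 / 0.75 = 296
- Invited: 296 / 0.42 = 704.8, about 705
- Check: 705 × 0.42 × 0.75 = 222.1

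Compared with the plan, this is 705 − 663 = 42 more invitations and 296 − 278 = 18 more randomised patients.

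**4. Other readings of 663.** If 222 were the number to randomise, with no allowance for dropout, the invitations would be 222 / 0.42 = 528.6, or 529. Dividing by 0.75 gives 705. Neither gives 663. The dropout at which 663 invitations would leave 222 is 1 − 222 / 278.46 = 20.3%, not 25%.

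**5. Effect on power.** The article does not say which repeated-measures test was used in G*Power or what correlation between measurements was entered, so this step rests on assumptions. I take the between-groups F-test with f = 0.25, k = 3 groups and m = 2 measurements. The significance level is 0.05/3 = 0.0167: the printed 0.167 does not fit the stated 5% overall error, and it plays no part in steps 1 to 4. The noncentrality is λ = f² × N × m / (1 + (m − 1)ρ), with 2 and N − 3 degrees of freedom.

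| Assumed ρ | Smallest balanced N for 90% | Power at 222 | Power at 209 |
|---|---|---|---|
| 0.5 | 198 | 93.9% | 92.2% |
| 0.6 | 210 | 92.1% | 90.1% |
| 0.7 | 222 | 90.2% | 87.9% |
| 0.8 | 234 | 88.1% | 85.7% |

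Of these, ρ = 0.7 returns 222 as the smallest balanced number, so it is a plausible reconstruction of the sponsor's input. It was, however, picked because it fits. The loss from 222 to 209 is 1.7 to 2.5 percentage points over the range.

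**The case against.** No reading of the section rescues 663, but there are good reasons to limit the weight of the point.

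- **The rates are forecasts.** They come from earlier studies and from a review of internet interventions for anxiety and depression. A dropout of 20.3%, or a response of 222 / (663 × 0.60 × 0.75) = 74.4% with dropout at 25%, would close the gap. This stands as a reason for a low severity. It does not make the printed arithmetic right.
- **663 is not a cap.** The Recruitment section has all eligible patients in the participating hospitals invited, and nothing says invitations stop at 663. A reader might infer that the trial will fall short of 222. The document does not support that; a shortfall follows only if invitations end at 663 and the forecasts hold.
- **Completers are not the only information.** The Statistical analyses section plans intention-to-treat with generalised estimating equations over the repeated measures, with missing data assumed missing at random. A patient lost after the 16-week assessment still contributes the two measurements on which the calculation is built. This stands against saying flatly that 90% power is lost. It does not remove the inconsistency, because the sample size section itself deducts the 25%.
- **The power figure depends on undocumented inputs.** A reader might infer that true power is 88%. That holds only at ρ = 0.7 with the between-groups test. At 0.5 or 0.6 power stays above 90% even with 209. Under the group-by-time interaction test with the same f, it is at least 99% at the correlations tried (0 to 0.8).

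A reader might also suspect a further loss because consent to the trial is a separate condition for randomisation. The article gives no consent rate. The consent forms are part of the invitation package, so the 70% or the 60% may already include consent. I make no claim on it.

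**Conclusion.** The invitation figure is wrong on the plan's own terms. With the stated 70%, 60% and 25%, 663 invitations give about 278 randomised and about 209 completers, 13 (6%) short of 222; the number consistent with 222 is about 705. This part needs no outside assumption. That the cause is multiplication by 1.25 is an inference, although it fits exactly.

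The consequence is modest: about 2 percentage points of power (90.2% to 87.9%) under the between-groups test, a significance level of 0.0167 and ρ = 0.7. Power at 209 lies between 92% and 86% for ρ from 0.5 to 0.8. The required 222, the allocation and the analysis are untouched. I rate this a minor correction.

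**What to change.** Correct the targets in the sample size section to 296 randomised (222 / 0.75) and about 705 invited (296 / 0.42), and print the intermediate steps so that the chain can be checked.

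If 663 is kept, state that about 209 completers are expected at the assumed rates. Then restate the power from the sponsor's own G*Power inputs, naming the test and the correlation. The power figures given here should not be copied into the protocol, because they rest on an assumed correlation.

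The first option costs 42 more invitation packages through the registry route already in use; the second costs a sentence and one rerun of the calculation. Neither changes the design or the analysis.
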